**Methods:**

This multicenter randomized controlled trial compares the effectiveness and cost-effectiveness of conventional PFMT versus biofeedback-mediated PFMT plus neuromuscular electrical stimulation (NMES) for postpartum symptomatic POP women. The primary outcome is the proportion of patients with the improvement of at least one POP-Q stage at 36 months after randomization. The primary economic outcome measure is incremental cost per quality-adjusted life year at 36 months. Two hundred seventy-four women from four outpatient medical centers are randomized and followed up with pelvic floor examination, questionnaires, and pelvic ultrasonography imaging. All participants are arranged for three appointments over 12 weeks. NMES and electromyography biofeedback via intravaginal probe are added to PFMT for participants in the biofeedback-mediated PFMT group. Group allocation could not be blinded from participants and healthcare staff that deliver intervention but remain masked from medical staff that carry out PFM assessment. An intention-to-treat analysis of the primary outcome will estimate the difference of the proportion of POP-Q stage improvement between the trial groups right after the intervention, and during the follow-up until 36 months, using the chi-square test and multilevel mixed models respectively. A logistic regression analysis was used for adjusting for important baseline variables that are unbalanced.

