## Methods

### Trial design {8}

PROSPECT (to treat *pro*lapse *s*uffered *p*ostpartum with *e*lectrical stimulation-*c*ombined *t*raining of pelvic floor muscle) study comprises a two-armed, multicenter randomized controlled trial (Fig. 1). We anticipate to recruit 274 eligible primiparas in the 6th postpartum weeks and randomly assign them (by sealed envelope) on a 1:1 ratio into an experimental group that receives NMES and EMG biofeedback-mediated PFMT and a control group that receives conventional PFMT alone. Group allocation could not be blinded from participants. Within a 3-year follow-up, we will continuously monitor the effect on POP by measuring:
Commonly mentioned POP-related symptoms with questionnairesAnatomic position of pelvic organs and morphology of pelvic floor through POP-Q staging and ultrasonographyPFM strength by digital palpation under the Modified Oxford ScalePFM electromyography employing the Glazer Protocol

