### Sample size {14}

Previous research has reported that 43.68~62.8% [31–33] of participants in the electrical stimulation plus PFMT group showed improvement in POP-Q staging while 15.4~20.9% [31–34] showed improvement in the PFMT group. Based on early-stage data from the ongoing pilot study, we estimate the proportion of participants with improved POP-Q stage to be 50% in the experimental group and 20% in the control group. Participants are randomized at a 1:1 ratio to the intervention and control groups. We applied a 2-sample superiority test on the proportions to calculate the sample size by PASS software. Based on our clinical treatment experience, we set the testing margin as 15% which indicates the significant clinical effectiveness. Assuming an attrition rate of 20% by the 36-month follow-up, a sample size of 284 women (142 in each arm) is required in the study to provide more than 80% power at a one-sided significance level of 0.05 for the 2-sample superiority test.

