### Assignment of interventions: allocation

#### Sequence generation {16a}

Following baseline examinations, participants will be randomly assigned to the experimental group or the control group (1:1 ratio). A random number sequence with a size of 274 and a planned seed number of 2 is generated using the SAS9.4 system.

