#### Concealment mechanism {16b}

The group allocation according to the random sequence is sealed in opaque envelopes, which is blinded to participants and research staff. New participants are sequentially numbered based on the chronological order of enrolment. Only then (after verification of eligibility, informed consent, and registration of enrolment) are they allowed to unwrap the corresponding envelope.

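### The sample size section requires 284 women, but the abstract, trial design and allocation sequence all use 274, which gives about 79% power on the plan's own inputs

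*Protocol article*

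**What the plan says.** Sample size {14} assumes the proportions improved "to be 50% in the experimental group and 20% in the control group". It adds a superiority margin ("we set the testing margin as 15% which indicates the significant clinical effectiveness"), a one-sided 5% level, 1:1 allocation and 20% attrition by 36 months, and concludes that "a sample size of 284 women (142 in each arm) is required in the study to provide more than 80% power".

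Three other places give a different size:

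- Abstract, Methods: "Two hundred seventy-four women from four outpatient medical centers are randomized".
- Trial design {8}: "We anticipate to recruit 274 eligible primiparas".
- Sequence generation {16a}: "A random number sequence with a size of 274 and a planned seed number of 2 is generated using the SAS9.4 system".

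Concealment mechanism {16b} ties each woman to an envelope by her place in the enrolment order: "New participants are sequentially numbered based on the chronological order of enrolment". Implementation {16c} says that an independent trial unit generates the sequence and that it is password-protected from the investigators. Nothing in the article explains the gap of 10 women or provides for allocations beyond number 274.

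**The concern.** The two figures cannot both be the planned size. Neither 284 nor 274 looks like a stray misprint: the per-arm figure of 142 confirms 284, and 274 appears three times, once spelled out in words. The figure that governs recruitment and the allocation list is the smaller one, and the power statement belongs to the larger one. If the trial runs as the design and randomisation sections describe, it closes 10 women (10/284 = 3.5%) below the size it calls necessary, and its power claim no longer describes it.

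A smaller matter sits in the same {16a} sentence. It discloses the list length, the software and the seed, which works against the password protection described in {16c}.

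**Working it through.** **Inputs**, all from Sample size {14}: experimental proportion 0.50, control proportion 0.20, margin 0.15, one-sided alpha 0.05 (z = 1.645), power 0.80 (z = 0.842), attrition 0.20, allocation 1:1. The variance formula is not named. The unpooled normal approximation is inferred because it reproduces the stated total.

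**Reproducing 284**

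- Variance term: 0.50 × 0.50 + 0.20 × 0.80 = 0.41.
- Distance from the margin: 0.50 − 0.20 − 0.15 = 0.15.
- Evaluable per arm: (1.645 + 0.842)² × 0.41 / 0.15² = 112.66, rounded up to 113.
- Allowing for attrition: 113 / 0.80 = 141.25, rounded up to 142 per arm, or 284 in total. This matches the stated figure exactly.

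**Power at each size**, from Φ(0.15 / √(0.41/n) − 1.645), with n evaluable women per arm:

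| Randomised | Attrition | n per arm | Power |
|---|---|---|---|
| 274 | 20% | 109 | 78.8% |
| 274 | 20% | 109.6 (137 × 0.8) | 79.0% |
| 274 | 20% | 110 | 79.2% |
| 284 | 20% | 113 | 80.1% |
| 284 | 20% | 114 | 80.4% |
| 274 | none | 137 | 86.4% |
| 284 | none | 142 | 87.4% |

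**Where 274 crosses 80%.** The formula needs 112.66 evaluable per arm, and 112.66 / 137 = 0.822. With 274 randomised, power falls below 80% only when attrition exceeds about 17.8%.

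**Sensitivity to the method**, at 20% attrition:

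| Method | 274 | 284 | Total needed for 80% |
|---|---|---|---|
| Unpooled, normal | 78.8–79.2% | 80.1–80.4% | 284 |
| Unpooled, exact enumeration | 78.4–79.2% | 79.3–80.0% | not computed |
| Restricted maximum likelihood variance | 77.2–77.5% | 78.5–78.8% | 296 |
| Pooled variance | 76.2–76.6% | 77.6–77.9% | 304 |

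All four put 274 below 80% under the stated attrition. Only the unpooled normal approximation puts 284 clearly above it.

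**The case against.** The strongest reply is that nothing of substance turns on ten women. The loss is about one percentage point, it disappears if attrition stays under about 17.8%, and it is measured with a formula the protocol does not name. The match to 284 is also not unique: the restricted maximum likelihood size of 118, multiplied by 1.2, gives 141.6, rounded up to 142 per arm, which is again 284. All of this stands, and it is why the point is a consistency correction. It does not remove the contradiction, since 274 misses the stated power under every method tried.

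A second reply is that 79% would not describe the planned analysis either. Statistical methods {20a} names a chi-square test and mentions no margin. For 50% against 20% that test has more than 99% power at either size. Section {20c} refers missing primary outcomes to baseline. If that means counting them as not improved, 20% attrition turns 50% and 20% into 40% and 16%, and power against the margin is about 53% at 274 and 54% at 284. This also stands as a limit: a restated figure must be labelled as applying to the margin test in evaluable women. The mismatch between test and calculation is a separate question and affects both sizes alike.

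A reader might infer more than the text supports:

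- *That 274 came from multiplying by 1.2 instead of dividing by 0.8.* The article does not say so, and 113 × 1.2 = 135.6, rounded up to 136, gives 272.
- *That staff would improvise allocations after number 274 and lose concealment.* Nothing suggests this. An independent unit generates the list and could extend it, and a trial that stops at 274 needs no further allocations.
- *That the list lacks blocks or centre strata and should be redesigned.* A condensed article is silent on this, and silence is not a finding.
- *That the published seed breaks concealment.* A seed without the program does not by itself give the list. Opaque envelopes opened only after eligibility, consent and registration remain in place. It is a weakening, no more.

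**Conclusion.** The contradiction is real. The protocol calls 284 necessary in one section and works to 274 in three others, without explanation. The larger figure follows exactly from the stated inputs under an unpooled normal approximation. The smaller one gives about 79% power (78.8% to 79.2%) where more than 80% is promised.

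The size of the shortfall rests on three assumptions: the full 20% attrition, the inferred formula, and the 15-point margin test in evaluable women. It would be wrong to call the trial materially underpowered on this ground, since the gap between the two sizes is about one point under every method checked. The point is a consistency correction. The seed disclosure is a minor addition.

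**What to change.** Use one number in all four places. Either of two routes resolves it:

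1. **Adopt 284.** Change the abstract, {8} and {16a} to 284 and have the independent unit extend the list by 10 allocations, using a seed that is not disclosed. The cost is 10 more women, whom the calculation already calls for, and one short run by the unit.
2. **Keep 274.** Change {14} to 274 (137 per arm) and restate power as about 79%, saying that this is for the test against the 15-point margin with 20% attrition. Name the variance formula. The cost is wording and giving up the claim of more than 80%.

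Either change is a protocol modification, which the oversight and amendment sections ({5d, 21a, 23} and {25}) send to the Ethics Committee. Trial status reports 75 women enrolled at the first centre and the other centres' applications still underway, so the correction can be made well before the two sizes diverge in practice. A seed already in print cannot be recalled, so the advice on an undisclosed seed applies only to allocations generated from now on.

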### Assignment of interventions: allocation

#### Sequence generation {16a}

Following baseline examinations, participants will be randomly assigned to the experimental group or the control group (1:1 ratio). A random number sequence with a size of 274 and a planned seed number of 2 is generated using the SAS9.4 system.

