#### Implementation {16c}

The allocation sequence is generated by a registered clinical trial unit in China that is independent and password-protected from the investigators. Their employees are specialized in statistics and uninvolved in the following process. The principal investigator in each center is responsible for the eligibility verification, informed consent implementation, and conduct of allocation revealment during the enrolment process.

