## Trial status

The internal pilot of the PROSPECT trial in Beijing Hospital (the first center of this study) has been approved by Ethics Committee and registered on the Chinese Clinical Trial Registry (ChiCTR2100021719). Its recruitment has begun in July 2020 and will terminate by December 2024. A total of 75 patients have been enrolled in our center (Beijing Hospital) and statistical analysis of their data is ongoing. Applications of other centers are underway. The current protocol has been refined on version 2 (approved on February 28, 2019). We apply the Standard Protocol Items: Recommendations for Interventional Trials (SPIRIT) to structure our protocol.

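### The protocol article publishes the software, length and planned seed of the allocation list while recruitment is open, so allocation concealment can no longer be assured

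*Protocol article*

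**What the plan says.** Sequence generation {16a} gives three of the inputs to the list: "A random number sequence with a size of 274 and a planned seed number of 2 is generated using the SAS9.4 system".

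Implementation {16c} describes the protection of that list: "The allocation sequence is generated by a registered clinical trial unit in China that is independent and password-protected from the investigators". The same section goes on: "The principal investigator in each center is responsible for the eligibility verification, informed consent implementation, and conduct of allocation revealment".

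Concealment mechanism {16b} relies on envelopes: "The group allocation according to the random sequence is sealed in opaque envelopes, which is blinded to participants and research staff". On the order of use it says: "New participants are sequentially numbered based on the chronological order of enrolment". The matching envelope may be opened only once eligibility, consent and registration are complete.

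Trial status reports on the internal pilot at the first centre: "Its recruitment has begun in July 2020 and will terminate by December 2024". It gives 75 women enrolled there and says the other centres are still applying. Who will be blinded {17a} states that participants and treating physiotherapists cannot be blinded, while pelvic floor assessors, data coordinators and analysts are.

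**The concern.** A seeded generator returns the same numbers to anyone who runs the same program. The seed is therefore the part of the list that most needs to stay private, and here it is in print, with the software version and the length, while women are still being enrolled. That works against the password protection claimed in {16c}. The people the list is meant to be hidden from can read this article. By the section on the coordinating centre {5d}, the principal investigators also help refine the protocol.

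Because treatment is open, concealment up to the moment of assignment is the main safeguard against selection at entry. Masked assessors protect the measurement of POP-Q stage but not the decision on whom to enrol and when. An investigator who could predict the next arm would have room to act on it. Recruitment {15} gives women several days to consider and then a telephone invitation, and the eligibility window covers the 6th to 8th postpartum week. A woman could be encouraged, booked later or not pursued according to the expected arm. Opening the envelope only after enrolment prevents a reaction to a revealed allocation, but not to a predicted one. Imbalance created this way cannot be reliably repaired in the analysis.

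**Working it through.** The plan states no figure for this point, so there is none to reproduce. The check has four steps.

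**1. What is disclosed and what is not.**

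| Needed to rebuild the list | Printed? |
|---|---|
| Software and version | Yes: SAS 9.4 ({16a}) |
| Length | Yes: 274 ({16a}) |
| Seed | Yes: 2, described as planned ({16a}) |
| Allocation ratio | Yes: 1:1 ({16a}) |
| SAS procedure or random-number function | No |
| Blocking or stratification, if any | No |
| Rule turning numbers into arms | No |

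The printed items do not determine the list. A rebuild would mean trying combinations of the last three rows.

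**2. Could a correct guess be recognised?** Assume simple 1:1 randomisation, and that the allocations already opened came, in order, from this list. A wrong candidate list then agrees with k known allocations with probability 0.5^k:

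- k = 10: 0.5^10 = 9.8 × 10⁻⁴
- k = 20: 0.5^20 = 9.5 × 10⁻⁷
- k = 75: 0.5^75 = 2.6 × 10⁻²³

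If someone tried 10,000 candidate programs against 20 known allocations, the expected number of false matches would be 10,000 × 9.5 × 10⁻⁷ ≈ 0.0095. A full match would therefore be convincing. Under blocking, wrong lists with the same block structure agree more often, so more opened allocations would be needed, but the logic is the same. If the opened allocations came from another list, this confirmation is not available.

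**3. Time open.** From 9 February 2022 to 31 December 2024 is 1,056 days. 1,056 / 365.25 = 2.89 years. The closing date is stated for the first centre's pilot; none is given for the other centres.

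**4. Allocations exposed.** If the 75 women count toward the list, 274 − 75 = 199 remained, and 199 / 274 = 72.6%. The Abstract spreads the 274 over four centres, so the 199 already include every allocation at the three centres not yet open. The sample size section asks for 284 rather than 274. That is a separate discrepancy and hardly changes the share: (284 − 75) / 284 = 209 / 284 = 73.6%. The 75 is the count when the status paragraph was written, which is undated, so 199 is an upper figure for the publication date.

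**The case against.** The strongest reply is that nothing shows the list can actually be rebuilt. A reader might infer from the printed seed that any investigator can regenerate the sequence and that concealment is already gone. The documents do not support that. The routine, any blocking and the number-to-arm rule are withheld. The seed is called planned, and the independent unit may have used another value. The text does not say that the 75 pilot women were allocated from this 274-long list, nor how the list is divided among centres. This part of the objection stands, and it limits the conclusion to a risk.

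A reader might also add the allocations at the three unopened centres to the 199, which would count them twice. Or a reader might put a figure on the bias in the treatment difference. That needs the share of enrolments steered and the prognostic difference between the women chosen for each arm, and the documents give neither.

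The objection does not remove the point. Concealment should hold without relying on investigators' restraint or on their not guessing a program. The envelopes do not help if their content can be predicted. The word planned does not settle the matter either, because no other seed is stated and the reader must take 2 as the intended value.

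**Conclusion.** The concern holds as a threat to concealment, not as proof that concealment has failed. Publishing the software, length and planned seed during recruitment conflicts with the protection claimed in {16c} and reduces the secret to a trial-and-error search. Allocations already opened could confirm that search if they came from the same list. Envelopes follow the order of enrolment, and one role at each centre verifies eligibility, takes consent and reveals the arm in an open-label trial. Concealment can therefore no longer be assured.

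The exposure is up to 199 of 274 allocations (73%) across the four centres at the time of the status statement, provided the 75 women count toward the 274. The resulting bias, if any, cannot be sized from the documents. The conclusion assumes that the published seed is the one in use. If it is not, the risk falls away and {16a} is simply inaccurate.

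**What to change.** - Have the independent trials unit regenerate all unused allocations with an undisclosed seed and, if blocks are used, an undisclosed block structure.
- Replace every unopened envelope with one from the new list.
- Remove the seed from the protocol, and keep seed and program code in a restricted file until recruitment closes.
- If the list in use was made with a different seed, say so and correct {16a}, again without disclosing the value.

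The cost is one list generation, reprinted envelopes (up to about 199 under the assumption above) and a short amendment. No extra participants, visits or assessments are needed. A comparison of women randomised before and after the change would not replace this: on the status given, the earlier group comes from one centre only and the later group would add three more, so the comparison would be confounded with centre.

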#### Concealment mechanism {16b}

The group allocation according to the random sequence is sealed in opaque envelopes, which is blinded to participants and research staff. New participants are sequentially numbered based on the chronological order of enrolment. Only then (after verification of eligibility, informed consent, and registration of enrolment) are they allowed to unwrap the corresponding envelope.

#### Implementation {16c}

The allocation sequence is generated by a registered clinical trial unit in China that is independent and password-protected from the investigators. Their employees are specialized in statistics and uninvolved in the following process. The principal investigator in each center is responsible for the eligibility verification, informed consent implementation, and conduct of allocation revealment during the enrolment process.

### Assignment of interventions: blinding

#### Who will be blinded {17a}

Due to the nature of the intervention, blinding of participants and physiotherapists delivering interventions or entering data is not possible but the research staff that carry out pelvic floor assessment, data coordinators, and analysts will be blinded to the group allocation result.

#### Procedure for unblinding if needed {17b}

Unblinding is not applicable.

### Data collection and management

#### Plans for assessment and collection of outcomes {18a}

Except for the past medical history that is only collected before and during the baseline visit, we will perform the rest of the items listed below in the baseline visit and follow-ups scheduled at and 6, 12, 24, and 36 months after the end of the intervention, to acquire primary and secondary outcome measures.
Past medical history. We collect the gestation and delivery information for a baseline from the hospital’s Electronic Medical Record System. The important prognostic covariates for the clinical effectiveness, including newborn weight, the length of first/second stage, infant head circumference, and maternal body mass index, will be recorded.Lifestyle information: the habits of smoking or drinking, and the frequency of moderate-intensity exercise, which is important covariates for the long-term effectiveness. POP-Q stage. Anatomical severity of pelvic organ descent is measured and staged in a POP-Q examination during each follow-up appointment.Prolapse symptoms. We document the presence of POP-related symptoms among participants in each follow-up appointment. Symptoms selected for inquiry are those frequently included in the validated questionnaires and reported by POP patients.Questionnaires. POP-related urinary, colorectal-anal, and pelvic symptoms are evaluated with Pelvic Floor Distress Inventory-Short Form 20 (PFDI-20) and sexual symptoms using Pelvic Organ Prolapse/Urinary Incontinence Sexual Questionnaire (PISQ-12). The impact of such symptoms on quality of life is assessed by the Pelvic floor Impact Questionnaire-Short Form 7 (PFIQ-7), Incontinence Impact Questionnaire-Short Form 7 (IIQ-7), and EuroQol Five Dimensions Questionnaire (EQ-5D). These questionnaires are instruments with evidence of validity, reliability, and responsiveness and have been translated into Chinese. Participants are referred to complete these questionnaires at the end of each follow-up appointment.PFM strength grade. PFM strength that reflects the muscle function is graded using the Modified Oxford Scale (MOS) in digital palpation during each follow-up appointment.PFM electromyography. Glazer Protocol consists of PFM EMG values in the pre-baseline, flick contraction, tonic contraction, endurance contraction, and post-baseline phases. Obtained in each follow-up, these EMG values indicate muscle activity from an electro-physiological perspective objectively.Pelvic ultrasonography. Three-dimensional ultrasonography is widely used to assess the morphology of the pelvic floor muscles and pelvic organs, including the diameter of levator hiatus and position of the bladder and rectum at rest and during maximum Valsalva.

To promote data quality, all the assessments are done independently by two physiotherapists who have been given sufficient training. Altogether, these examinations comprehensively evaluate the morphology and function of PFM as well as the anatomical and clinical evidence of POP severity. Data collection forms are attached in the protocol.
Economic analysis (cost-effectiveness analysis). The primary analysis will be undertaken alongside the trial using recommended methods [35, 36]. All costs and outcomes beyond 1 year will be discounted at 3.0% [37]. Incremental cost-effectiveness ratios (ICERs) will be computed by comparing the costs and effectiveness under the interventions of each group. The difference in effectiveness will be measured as the change in the proportion of the patients showing improvement of at least 1 level of POP-Q staging. The difference in cost-utility between the two groups will be expressed in terms of quality-adjusted life years (QALYs) that is calculated from the EQ-5D scores [36] using the actual time of follow-up. Multiple imputation is used to replace missing data. Analyses of total costs and QALYs use adjustments for baseline covariates via seemingly unrelated regression, and the final data is used to plot data on the cost-effectiveness plane.

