#### Plans to promote participant retention and complete follow-up {18b}

Measures to help participants cling to the established schedule include:
Seven days prior to their scheduled appointments, participants will receive a reminder message or email where they are notified of the accurate time, place, and recommended preparations for each procedure performed in that duration and they are asked to confirm their attendance. Those who do not reply to the message will receive a phone call.If participants report difficulties in arriving for follow-ups, shortage of time, or inconvenient traffic for example, we will try our best to give assistance, such as adjusting their schedule as long as the time window for each follow-up is not exceeded.We will contact participants who forget to return their questionnaires or miss other examinations within a week to see if they need reminders or other forms of help in the future.

If for any reason they opt to withdraw, no more intervention will be conducted, and no more data will be collected. Data collected before their dropout is used for further analysis under their consent. They will be invited to complete a questionnaire on the reasons for quitting.

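### Five self-report questionnaires, including the EQ-5D behind the QALYs, are completed by unblinded women at the end of each follow-up visit, after the vaginal examination; they should come first

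*Protocol article*

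**What the plan says.** All statements are in the Protocol article.

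- **Questionnaires.** Section {18a} names five instruments (PFDI-20, PISQ-12, PFIQ-7, IIQ-7, EQ-5D) and fixes when they are filled in: "Participants are referred to complete these questionnaires at the end of each follow-up appointment".
- **Examinations.** The same section says of POP-Q: "Anatomical severity of pelvic organ descent is measured and staged in a POP-Q examination during each follow-up appointment". Muscle strength is "graded using the Modified Oxford Scale (MOS) in digital palpation during each follow-up appointment". On EMG it says: "Obtained in each follow-up, these EMG values indicate muscle activity from an electro-physiological perspective objectively". Ultrasound has no timing of its own and falls under this general rule: "we will perform the rest of the items listed below in the baseline visit and follow-ups scheduled at and 6, 12, 24, and 36 months". Those months count from completion of treatment.
- **Blinding.** Section {17a} states that "blinding of participants and physiotherapists delivering interventions or entering data is not possible". It adds that "the research staff that carry out pelvic floor assessment, data coordinators, and analysts will be blinded to the group allocation result".
- **Use of the scores.** Change from baseline in each of the five instruments is a secondary outcome (Secondary outcomes, under Outcomes {12}). The economic paragraph of {18a} derives QALYs from the EQ-5D, and the Abstract makes cost per QALY at 36 months the primary economic outcome.

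**The concern.** Self-report is the part of the data that assessor blinding cannot protect, because the woman herself is the assessor and she knows her arm. Putting the forms last adds a second influence. By the time she answers, she has been examined vaginally and may have learned, from a remark or a display, whether her prolapse or muscle function has improved. Her answers on symptoms, impact and current health may then partly reflect that information.

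If so, the questionnaires would be weaker as independent support for the anatomical result. The Background says that earlier studies judged response mainly by symptoms and that this trial adds objective measures. That pairing is worth most when the two kinds of data are collected independently. Through the EQ-5D, any distortion would also enter the cost per QALY.

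**Working it through.** There is no figure in the plan to reproduce here. The check is a reading of the order of assessment and of what a between-arm bias would need.

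**Step 1: order within the visit**

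| Item | Position stated in {18a} | Relation to the questionnaires |
|---|---|---|
| Five questionnaires | End of each follow-up appointment | – |
| POP-Q examination | During the appointment | Before |
| Digital palpation | During the appointment | Before |
| EMG | At each follow-up, no position given | Before, by inference, if done at the same visit |
| Ultrasound | At the scheduled follow-ups, no position given | Before, by inference, if done at the same visit |
| Symptom inquiry | In each follow-up appointment, no position given | Unknown |

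The order is firm for POP-Q and palpation. For EMG and ultrasound it follows only from the word end. Section {18b} foresees some late forms: "We will contact participants who forget to return their questionnaires or miss other examinations within a week". A form returned after the visit is still completed after the examinations.

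**Step 2: could findings reach the woman first?** No statement says that results are disclosed before the forms, and none says that they are withheld. Some contact that could convey progress is planned. Section {11b} has training programmes modified in follow-up appointments according to muscle performance, and {11a} has the physiotherapist adjust the programme at the appointments during the intervention, the last of which is at week 12.

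**Step 3: would the effect differ between arms?** The order is the same in both arms, so order alone cancels. A between-arm difference needs findings that differ by arm and become known, or an interaction with knowledge of allocation. The first is plausible under the plan's own assumption of 50% versus 20% improved (Sample size {14}), a gap of 0.50 − 0.20 = 0.30.

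**Step 4: can it be sized?** Let *d* be the shift in a score, in SD, from learning that the stage improved, and let *r* be the proportion of improved women who learn this before answering, taken as equal in both arms. The spurious difference is then

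bias = *d* × *r* × (0.50 − 0.20) = 0.30 × *d* × *r*.

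The document gives neither *d* nor *r*. With *r* = 0 the bias by this route is zero. No value can be derived.

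**Step 5: what is affected?** The five questionnaire scores and the EQ-5D-based QALYs are. POP-Q stage is not: blinded staff measure it, and it does not depend on when the forms are filled in.

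**The case against.** The strongest case against has four parts.

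1. **The visit sequence may be condensed.** The schedule in Fig. 2 is not shown, and details of all procedures are assigned to an SOP manual (Eligibility criteria for healthcare providers). This stands for EMG and ultrasound. It does not stand for the questionnaires, whose place at the end is stated outright.
2. **The mechanism is conjecture.** Nothing documents that a woman is told her result before answering. This stands, and it makes the point one of risk.
3. **Reordering leaves the larger threats.** Knowledge of allocation is unavoidable, a result learned at one visit is still known at the next, and the experimental arm follows visual EMG feedback in its 24 sessions. This stands too. It limits what the change can achieve, but is no reason to keep an avoidable influence.
4. **Switching now mixes two orders.** Trial status reports 75 women enrolled at the first centre. This is a real but small cost, and it can be handled in the analysis.

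A reader might infer more than the document supports:

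- *That every patient-reported outcome is affected, or that these forms are the only measure of symptoms.* Outcomes {12} lists the proportion with each symptom as a separate secondary outcome, and {18a} gives that inquiry no position in the visit.
- *That the bias has a known size.* Assuming *d* = 0.2 to 0.5 SD and *r* = 1 gives 0.30 × 0.2 = 0.06 SD to 0.30 × 0.5 = 0.15 SD. The range for *d* has no source, *r* = 1 assumes every improved woman is told, and the sum counts only good news and presumes that the planned rates come true.
- *That baseline is defective.* The sentence covers follow-ups only, and {16a} randomises after the baseline examinations.
- *That end-of-visit timing causes forms to go unreturned.* Section {18b} is a retention safeguard and makes no such link.

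**Conclusion.** The point holds for five named questionnaires at follow-up. Unblinded women complete them after POP-Q staging and digital palpation, and by inference after EMG and ultrasound if these are done at the same visit. Nothing shown keeps findings from them until the forms are done. The examination or its result could therefore influence these secondary outcomes and the EQ-5D-based QALYs behind the primary economic outcome.

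The size cannot be derived from the document, and no bias is demonstrated. The conclusion rests on reading the stated end of the appointment as after the examinations made during it, and on the absence of any shown safeguard. The primary clinical outcome and the sample size are untouched. The change is worth making because the plan fixes the less favourable order when the better one costs almost nothing.

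**What to change.** Change the sentence in {18a}, and the SOP to match, so that women complete and hand in all five questionnaires at the start of each follow-up visit, before any examination and before any result is discussed. State the same order for baseline, so that change scores compare answers given under the same conditions. If Fig. 2 or the SOP shows a sequence within the visit, bring it into line.

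The cost is a change of visit order, with no added procedure. Only the first centre had enrolled when the article was written and applications for the others were underway, so most follow-up can still use the new order. For women already enrolled in the pilot, record the order used at each visit, or the date of the switch, and check its influence on the questionnaire and QALY results in a sensitivity analysis.

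The report should claim no more than the change delivers: it reduces one avoidable source of bias, and does not remove bias from knowledge of allocation or from results learned at earlier visits.
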